Hormonal dysfunction following pTBI is common and can evolve, resolve, or persist after injury [31]. It is not clear how much of the puberty related hormonal changes contribute to variation in pTBI outcomes [31]. Puberty is a key developmental milestone accompanied by substantial physical growth, neurologic changes, peak levels of sex hormones, and changes in emotional and behavioral symptoms [32]. It encompasses a combination of two distinct brain activated hormonal processes, adrenarche (the activation of the HPA axis) and gonadarche (the reactivation of the hypothalamic-pituitary-gonadal axis), which together lead to a dramatic rise in the circulating levels of sex hormones [33]. Puberty is associated not only with an increase in hormone levels, but also with dramatic fluctuations in the levels of estrogen circulating in the body [34]. Subsequently, the body’s systems must rapidly adapt to higher and fluctuating levels of hormones that may influence mood and other emotional symptoms. Recently, a large cohort study [35] demonstrated that earlier onset of puberty (pubescence) was associated with higher risk of depression and anxiety in females but was unrelated to the presence of depression in males. The gap between the onset of emotional changes and full maturation of inhibitory brain mechanisms may contribute to a window of risk for emotional dysregulation and other neuropsychiatric symptoms during puberty [36]. Paucity of studies have indicated that pubertal status predicts sex difference in the prevalence of neuropsychiatric symptoms better than age, suggesting that sex hormones play a significant role in the pathophysiology of neuropsychiatric disorders [34]. Furthermore, it should be acknowledged that age and pubertal maturation are highly correlated, arising the need for research designs that explicitly disentangle puberty and age effects on pTBI outcomes [37]. This requires the comparison between females with and without pTBI within the same age range and puberty phase.

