### Aims and hypotheses

Based on the literature review, the present study proposes the following aims and hypotheses (as depicted in Fig 1):

**Aim 1**: Examine the moderating effect of puberty (pre- and post-pubescence) on the association between pTBI, brain network connectivity measures and neuropsychiatric outcome among females:

1.1. Examine the direct association between pTBI and neuropsychiatric outcome (Fig 1: direct effect c’ pathway). We hypothesize that females following pTBI will present poorer neuropsychiatric outcome as compared to healthy female controls.

1.2. Examine the relationship between pTBI and brain network connectivity measures (Fig 1: slope a pathway). We hypothesize that females with pTBI will present higher network connectivity measures and lower network efficiency compared to healthy female controls.

1.3. Examine the relationship between brain network connectivity measures and neuropsychiatric outcome (Fig 1: slope b pathway). We hypothesize that higher network connectivity measures and lower network efficiency will be associated with poorer neuropsychiatric outcome.

1.4. Examine the moderating effect of puberty on the mediated association between pTBI, brain network connectivity and neuropsychiatric outcome (Fig 1: mediation a*b pathway through moderator). We hypothesize that puberty will moderate the associations between brain network connectivity measures and network efficiency, and neuropsychiatric outcome in females post pTBI. That is, post-pubescence females compared to pre-pubescence females will show higher network connectivity measures, lower network efficiency and poorer neuropsychiatric outcome.

**Aim 2:** Examine the effect of changes in puberty stage and hormonal levels on brain network connectivity measures and neuropsychiatric outcome in pTBI females. We hypothesize that among females following pTBI, earlier changes in puberty stages (i.e. changes from one Tanner stage to another) and a significant increase in hormonal levels across recovery, will be related to higher network connectivity measures and lower network efficiency as well as to poorer neuropsychiatric outcome.

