### Sample size and power

Sample size was calculated on the basis of our primary hypothesis that puberty will moderate the associations between brain network connectivity measures, and neuropsychiatric outcome in females post pTBI. The bootstrap method for moderated-mediation models was used [49]. The bootstrap method, based on resampling, is useful for finding the standard errors and forming percentile-based confidence intervals (CIs) for estimates when their sampling distributions are unknown. According to Preacher, Rucker & Hayes (2007), a minimum of 100 participants are required in order to achieve power of at least .80, at a significance level of α = .05, with a Cohen’s d medium effect size (corresponding to a value of 13% of the variance in predicted variable [50]; and in accordance with previous studies on neural correlates of neuropsychiatric outcomes in children with TBI [51]). Based on the literature on longitudinal studies with pTBI patients, and due to technical issues such as unusable scans due to excessive movement anticipated in a pediatric study, we anticipate an attrition rate of ≈20% [52]. Thus, 120 female participants will be recruited: 60 with pTBI and 60 healthy controls.

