#### 2. Moderator

*Pubertal stage*. Pubertal stage will be assessed at injury/first visit for controls (T0), and at 18 months from T0 (T1). Pubertal stage will be defined based on 3 different measures, known to be highly correlated [58]: (1) the Pubertal Development Scale (PDS) [59]. This self-report questionnaire contains questions concerning secondary sexual characteristics, including items concerning hair growth, skin changes, and growth spurt, with sex-specific items (i.e. menarche and breast development in females). The PDS measures a composite puberty score including effects of adrenal, and gonadal hormones, as well as growth hormone. Participants will be instructed to indicate pubertal stage on each of these physical characteristics on a 4-point scale: ranging from (a) has not started to develop, (b) shows first signs of development, (c) shows clear development to (d) has finished developing; (2) *Hormonal Levels* (LH, FSH and Estradiol) will be drawn from blood samples at T0 and T1. For females who are post menarche, and T1 assessment meetings will be scheduled at 3–5 days of the menstrual cycle; and (3) *Tanner Stage* assessment according to a physical examination conducted by a qualified clinician. Tanner staging categorizes individuals along an ordinal puberty scale from 1 to 5, on the basis of pubic hair and breast development in females [60]. The majority of girls reach Tanner Stage II at age 10.5 (a proxy for pubertal onset), and then progress through an average rate of 0.96 stages per year [61]. A binary puberty (pre and post-pubescence) score at T0 will be computed out of the pubertal stage measures and used as the moderator variable in the statistical model. If the different measures will conflict (i.e., yield different puberty stage classifications), the final score will be based on the Tanner stage score, which will be further used in analyses [47].

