### Analytical approach

The following analyses will be conducted on both pTBI patients and healthy controls:

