#### Descriptive statistics

Descriptive statistics of variables will be obtained to understand the characteristics of the study population, to evaluate the distribution of participants across subgroups (e.g., puberty stage), and to identify potential confounders to inform subsequent analyses.

**Aim 1**- **moderated-mediation model:** To test our main study’s hypothesis we will apply a moderated- mediation model. Briefly, we will examine whether the magnitude of a mediation effect impact of mediator (*changes in brain network connectivity*) on the association between predictor (*pTBI*) and outcome (*neuropsychiatric outcomes*) is conditional on the value of a moderator (*puberty stage at T0*). The analysis of the moderated-mediation model will use Hayes’s (2013) PROCESS macro (Model 59) [73]. Bootstrapping method will test significance of the effects to obtain robust standard errors for parameter estimation [73]. This will produce 95% bias-corrected confidence intervals of these effects from 1000 resamples of the data. Confidence intervals that do not contain zero indicate significant effects at *p* < .05.

**Aim 2- effect of changes in puberty stage and hormonal levels on mediator and outcome:** Two step-wise linear regression models controlling for age and pre/post-injury factors in the 1st step; for the injury severity in the 2nd step; and for puberty stage and hormonal levels at T0 and T1, as well as the difference between both measures (i.e., *Δpuberty stages and Δhormonal levels*) in the 3^rd^ step, to predict (1) brain network connectivity and (2) neuropsychiatric outcomes, at T1 will be conducted.

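### Aim 2 enters each puberty measure at T0, at T1 and as their difference in one step, so the change effects cannot be estimated as written, and no test is named for them

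*Protocol article*

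**What the plan says.** The Aim 2 paragraph (protocol article, Analytical approach, under Descriptive statistics) specifies "Two step-wise linear regression models controlling for age and pre/post-injury factors in the 1st step". Injury severity is added in the second step. The third step adds puberty stage and hormone levels at both visits together with their differences. The two models predict T1 brain network connectivity and T1 neuropsychiatric outcome.

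The aim itself (Aims and hypotheses) is to "Examine the effect of changes in puberty stage and hormonal levels on brain network connectivity measures and neuropsychiatric outcome in pTBI females", and its hypothesis is about change. The lead-in to the Analytical approach says something different about who is analysed: "The following analyses will be conducted on both pTBI patients and healthy controls".

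On the predictors, section 2. Moderator lists three hormones (LH, FSH, estradiol) and says "Pubertal stage will be defined based on 3 different measures, known to be highly correlated". The Introduction adds that "it should be acknowledged that age and pubertal maturation are highly correlated".

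The only sample-size statement is tied to the primary moderation hypothesis: "a minimum of 100 participants are required in order to achieve power of at least .80", and "120 female participants will be recruited: 60 with pTBI and 60 healthy controls".

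**The concern.** A difference entered beside its two components carries no new information. The regression has no unique solution, so the software decides which terms survive, often by order of entry.

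That choice matters. Write the fitted contribution of one measure as a·T0 + b·T1, with Δ = T1 − T0.

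- If T0 and Δ are kept, it becomes (a + b)·T0 + b·Δ, and the change coefficient is b.
- If T1 and Δ are kept, it becomes (a + b)·T1 − a·Δ, and the change coefficient is −a.
- If T0 and T1 are kept, no change coefficient is reported at all.

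The fit is identical in all three cases. The reported effect of change can still differ in size and sign, or be absent. Aim 2 is a hypothesis about change, so its main result would rest on a software default. The text also names no test for the aim, and the candidate tests differ considerably in power.

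**Working it through.** **Plan's own figure.** No sample size or power is stated for Aim 2. The only figure is the 120 set for Aim 1, which equals 100 × 1.20. A 20% loss leaves 120 × 0.8 = 96.

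**Terms**

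| Step | Content | Entered | Estimable |
|---|---|---|---|
| 1 | Age, SES, maternal education, ethnicity, religiosity, GHQ-12, pre-injury CBCL | 7 | 7 |
| 2 | Injury severity index | 1 | 1 |
| 3 | (Stage + LH + FSH + estradiol) × (T0, T1, difference) | 12 | 8 |
| Total | | 20 | 16 |

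Step 1 takes its factors from section 4. Covariates and assumes one df each. Step 3 assumes one stage score and hormones entered singly. A rank check on simulated 20-column data gave rank 16. The loss of four is exact and does not depend on the correlations assumed.

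**Girls.** On the pTBI-only reading, 60 × 0.8 = 48, which is 48/16 = 3 girls per estimable term. Residual df = 48 − 16 − 1 = 31.

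**Power.** Noncentral F test of an R² increase, α = 0.05, λ = n × f². The Sample size section gives the effect as 13% of variance, for Aim 1. It can be read in two ways:

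- Partial R²: f² = 0.13/0.87 = 0.149, λ = 48 × 0.149 = 7.17.
- Added R² over a base explained by the other terms: f² = 0.13/(1 − base − 0.13). The base is not in the document. At 20%, 30% and 40%, f² = 0.194, 0.228 and 0.277, and λ = 9.31, 10.95 and 13.28.

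| Test (n = 48, 31 residual df) | Partial R² 13% | Base 20% | Base 30% | Base 40% |
|---|---|---|---|---|
| Whole step-3 block, 8 df | 34% | 44% | 52% | 61% |
| Four change terms jointly, 4 df | 48% | 61% | 69% | 78% |

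The second row assumes that the four change terms carry the whole 13%. If they carry half (6.5%) and the T0 terms the other half, f² = 0.065/(1 − base − 0.13), and the 4-df test has 32%, 38% and 45%. With the stricter convention λ = f² × (u + v + 1), where u and v are the test and residual df, the partial-R² column falls to 28% and 37%.

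**If both groups were analysed** (n = 96, 79 residual df), the 8-df block has 73% on the partial-R² reading and 85%, 91% and 96% on the added-R² reading.

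**Does removing terms help?** A 2-df test of change in stage and change in one hormone measure has 75%, 82% and 89% in a 12-term model. The same test inside the 16-term model has 74%, 81% and 88%. The difference is about one percentage point.

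**The case against.** - **Term count.** The Aim 2 paragraph does not list the covariates, and it does not say that the three hormones enter one by one. A fuller analysis plan may settle both. This stands against the figures of 20 and 16, but not against the aliasing: any measure entered at T0, at T1 and as a difference is redundant. The power figure is also fairly insensitive to the covariate count. With only age and severity as covariates, block power on the partial-R² reading is 35%.
- **Number of girls.** The lead-in points to both groups, and at 96 the block test is adequately powered on most readings. The attrition allowance also covers unusable scans, which the model for neuropsychiatric outcome does not need, so 48 may be low for that model. Both points stand. The aim and its hypothesis are nonetheless written for pTBI girls, and the severity index is defined only for them.
- **Effect size.** The 13% is stated for Aim 1, and the base R² is assumed. This stands, and the power figures are therefore a range.
- **Separate models.** Secondary analyses already plan to look at each puberty measure separately. This is true, but it does not repair the main Aim 2 model.

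A reader might infer that the sheer number of terms causes the low power and that pruning would restore it. The last comparison in the working shows otherwise: the gain comes from the test chosen and from placing the whole effect in fewer terms. A reader might also infer that every single coefficient is uninterpretable. The document reports high correlation only among the puberty measures and between puberty and age. It gives no figure and says nothing of the family covariates. Outside the aliased terms, the extent of variance inflation is unknown. Nor would a high R² from many terms mislead the increment test, because the F test allows for its degrees of freedom.

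**Conclusion.** The third step of the Aim 2 model is wrongly specified. Stage and hormones at T0, at T1 and as differences are exactly redundant, and the hypothesised change effects depend on which terms the software keeps. This needs no assumption about correlations, effect size or sample size.

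The power result is conditional. It rests on pTBI girls only (about 48), about 16 estimable terms and a 13% effect borrowed from Aim 1. The whole-block test then has 34%, or 44–61% on the added-R² reading. A joint test of the four change terms has 48%, or 61–78%, and less if the effect is shared with the T0 values. Apart from the added-R² 4-df test near the 40% base, these are clearly below 80%, so Aim 2 should be presented with that limitation. The documents do not support one headline figure such as even odds, because the answer depends on the test and the plan names none.

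**What to change.** 1. In step 3, enter only the T0 value and the change for each measure, and drop the T1 values. No information is lost, since T0 and change together determine T1.
2. Name one joint F test of the change terms as the Aim 2 result for each of the two models (4 df with stage and three hormones). Do not interpret single coefficients among puberty measures that the protocol itself calls highly correlated.
3. State that Aim 2 is analysed in pTBI girls only, and reconcile the aim with the Analytical approach lead-in.
4. Optionally, replace the three hormones with a prespecified composite, which reduces the joint test to 2 df. On the partial-R² reading its power is about 63%, if the two change terms carry the whole 13%. The cost is less detail on single hormones, which can go into secondary models. The documents give no ground for choosing one hormone over the others.

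Items 1 to 3 are changes of wording. Recruitment, visits and data collection stay as they are.

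### Step 3 of both Aim 2 regressions enters each puberty and hormone measure at T0, at T1 and as their difference, so no separate coefficient for change is identified

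*Protocol article*

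**What the plan says.** The Aim 2 model is described under Analytical approach, in the Aim 2 paragraph of the Descriptive statistics subsection. It is built in ordered blocks: "Two step-wise linear regression models controlling for age and pre/post-injury factors in the 1st step", then injury severity in the second step. The third step controls "for puberty stage and hormonal levels at T0 and T1, as well as the difference between both measures", and the text spells out that difference as "Δpuberty stages and Δhormonal levels". The models are fitted "to predict (1) brain network connectivity and (2) neuropsychiatric outcomes, at T1 will be conducted".

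The Moderator section gives the measures. Three hormones are taken at both visits ("LH, FSH and Estradiol) will be drawn from blood samples at T0 and T1"), and for puberty stage, "Tanner staging categorizes individuals along an ordinal puberty scale from 1 to 5".

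Aims and hypotheses states the purpose of Aim 2: "Examine the effect of changes in puberty stage and hormonal levels on brain network connectivity measures and neuropsychiatric outcome in pTBI females". The hypothesis beneath it is directional: earlier stage transitions and rising hormone levels should go with higher connectivity, lower efficiency and poorer outcome.

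On who is analysed, the lead-in to Analytical approach says: "The following analyses will be conducted on both pTBI patients and healthy controls".

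**The concern.** A variable and its two components cannot all have their own coefficient in one linear regression. Aim 2 is about the coefficient for change, and that is the coefficient the written model cannot supply. An analyst following the text would have to drop one term per measure, or let the software do so, and the protocol does not say which. The choice decides what the remaining change coefficient means and can reverse its sign, without altering the fit. A directional hypothesis would then be supported or contradicted by something nobody had prespecified.

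A smaller matter concerns the same model. The lead-in puts both groups into the analysis, the aim is set in pTBI females, and the second step uses a severity index that has no stated value for controls.

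**Working it through.** **Inputs.** Terms in step 3: T0, T1 and their difference, for puberty stage and hormone levels (Aim 2 paragraph). Measures: Tanner stage plus three hormones, so 4 (Moderator section). The protocol prints no figure for this point that could be reproduced.

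**Algebra.** Write Δ = T1 − T0 for any one measure. Then

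b0·T0 + b1·T1 + bΔ·Δ = (b0 − bΔ)·T0 + (b1 + bΔ)·T1.

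Only b0 − bΔ and b1 + bΔ are determined by the data, and bΔ can take any value. Subtracting in the other order gives the same dependency with the sign of Δ changed.

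**Count.** 4 measures × 3 terms = 12 columns. One dependency per measure leaves 12 − 4 = 8.

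**Numerical check.** A simulated design had an intercept, age, one pre-injury factor and severity (4 columns) plus the 12 step-3 columns, 16 in all. Its rank was 12 at n = 48, 60, 96 and 120, that is 16 − 4 each time. Standardising the predictors left the rank at 12. Other codings of puberty stage do not help:

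- Tanner stage as dummy variables at both visits: a numeric Δ adds nothing (rank 12 without and with it at n = 60).
- A binary pre/post score at both visits plus its difference: 7 columns, rank 6 at n = 60.

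**What happens when a term is dropped.** Let the model with T0 and T1 have coefficients β0 and β1.

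- T0 kept, T1 dropped: β0·T0 + β1·(T0 + Δ) = (β0 + β1)·T0 + β1·Δ. The coefficient on Δ is β1.
- T1 kept, T0 dropped: β0·(T1 − Δ) + β1·T1 = (β0 + β1)·T1 − β0·Δ. The coefficient on Δ is −β0.
- Δ dropped: no coefficient for change is printed.

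The first two have opposite signs whenever β0 and β1 share a sign. In one simulated data set for puberty stage (n = 60, true values 0.5 for T0 and 0.8 for T1), the estimates with T0 and T1 in the model were 0.536 and 0.960:

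| Terms kept | Coefficient on Δ | R² |
|---|---|---|
| T0, T1 | none | 0.727 |
| T0, Δ | 0.960 | 0.727 |
| T1, Δ | −0.536 | 0.727 |

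The data and the fit are the same in every row, but the change effect has opposite signs in the last two. The size of these numbers comes from the simulation. The pattern follows from the algebra.

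**Population, side by side.** Aims and hypotheses: Aim 2 concerns pTBI females. Analytical approach: all the analyses that follow use both groups. Clinical TBI group: severity is an index from coma scale, post-traumatic amnesia and loss of consciousness, running from complicated-mild to severe, with no value given for a healthy girl. The Aim 2 paragraph lists no term for group. These statements do not describe one model.

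**The case against.** The strongest reply is that this is a redundant term and not a failed analysis. The models with T0 and T1, T0 and Δ, or T1 and Δ are one model in three forms, and the R² change for step 3, a usual output of block regression, is the same in all of them. That stands. A reader might infer that the effect of change cannot be estimated at all. The documents do not support this: the effect of change given the starting level is available once T0 and Δ are named as the terms. But the R² change does not rescue the text as written, because it combines level with change and has no sign.

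Other replies carry less weight. If step-wise means automatic selection, at most two of the three terms can enter, and the data or software choose them. The wording assigns variables to three ordered steps, which reads as blocks. A difference on another scale (for example raw differences beside log levels) would break the exact dependency, but no transformation is stated. The structural equation model is exploratory and takes its structure from the primary findings, so it does not replace this regression.

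On controls, a reader might infer that listwise deletion will remove every one of them. The protocol states neither a missing-data rule for this model nor a severity code for controls, so that is a guess about implementation. A reader might also object that a pTBI-only model cannot separate normal maturation from an effect of injury. Aim 2 asks how change relates to outcome among patients and claims no contrast with controls. The number of predictors relative to patients is a question of overfitting and says nothing about this defect.

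**Conclusion.** The concern holds in this form: as written, step 3 of both Aim 2 regressions has one exact dependency per measure (12 columns of rank 8 for the four measures counted here), and no separate coefficient for change is identified. A larger sample does not help. The count of 12 and 8 assumes Tanner stage as the puberty score, all three hormones entered together and a plain difference on the scale of the entered terms. A different puberty score changes the count but still leaves one dependency per measure.

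The consequence is an unspecified choice that can set the sign of the effect Aim 2 is about. It affects one of the two stated aims. The Aim 1 moderated-mediation model, on which the sample size rests, is untouched. The Aim 2 paragraph names no software, so which term would be dropped cannot be predicted. The disagreement over population is a real inconsistency to reconcile, but the text does not show that controls will be lost.

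**What to change.** 1. In step 3, enter T0 and Δ only for each measure, remove the T1 terms, and define Δ as T1 minus T0. State that the Δ coefficient, the effect of change given the starting level, is the Aim 2 test. The fit is identical to a model with T0 and T1, so nothing is lost.
2. Reconcile the lead-in to Analytical approach with Aim 2 and with the severity term. The simplest course is to state that Aim 2 is fitted in the pTBI group, which matches its stated question. If controls are to be included, say how severity is coded for them and add a pTBI main effect. Without it, coding severity as 0 in controls and centring it in patients would treat controls as patients of average severity.

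Both are wording changes that can be made before analysis. They need no new data and no change to visits or sample size. Including controls would cost the extra group term.

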### Research design

The proposed study will use a longitudinal prospective design and follow females after pTBI and age matched healthy female controls, aged 9 to 16 years [47]. Participants will be followed from admission to 18 months post injury. Participants will undergo an MRI protocol, a short neuropsychiatric assessment and a clinical assessment of puberty stage and hormonal level, across two time points: **Acute (T0)**: within one month post injury; **Chronic (T1)**: 18 months from T0 (sufficient time for neuropsychiatric changes post pTBI [48]). For a description of the schedule of study’s enrolment and assessment periods see S1 Table.

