### Mediator

#### Changes in network brain connectivity

A score indicating differences in brain network connectivity measures between T1 and T0 will be defined and used as the mediating variable in all analyses. Children will be scanned on a 3T Magnetom Prisma (Siemens Healthineers) MRI system. Structural scans, T1-weighted, fluid attenuation inversion recovery (FLAIR) and susceptibility-weighted imaging (SWI) will be acquired for clinical neuroradiology report. During scans, participants will watch animated videos, in order to achieve better compliance in the scanner.

*Structural connectivity*. Will be measured using a diffusion weighted imaging scan. Spin-echo diffusion-weighted, echo-planar imaging sequence will be performed with 76 axial slices, voxel size 2x2x2mm, FOV = 240x240, matrix = 120x120, TR = 4500ms, TE = 51ms, MB = 2; b-value = 1,000 s/mm^2^, 64 gradient directions, 3-b0 images. Regularization, brain extraction, and motion correction will be conducted. Diffusion tensors will be calculated using a nonlinear regression procedure [53]. Whole brain tractography will be performed based on deterministic streamline fiber tractography approach [54].

*Brain network architecture of structural connectivity*. Using Brain connectivity toolbox, structural connectivity matrices will be calculated, by which, nodes indicating anatomical elements (brain regions) and edges, representing the relationships between nodes (white matter tracts), will be defined. These connectivity matrices will be further used for graph theory analyses, allowing to quantitatively characterize the global organization via network measures [55]: (1) **centrality**: strength (number of fibers connected to each node) and betweenness centrality (number of shortest paths passing through the target node); (2) **integration**: global efficiency (the shorter the path between two regions, the more efficient the connection), and (3) **segregation**: local efficiency and cluster coefficient: (reflects the tendency of nodes to cluster together). Lesions will be classified using a scheme of Adams et al. (1989) [56], to identify 3 diffuse axonal injury grades. We will further assess the relationships between network measures and the lesion grading score [57].

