#### Secondary analyses

For all analyses, an equal distribution assumption of potential confounders (participants’ age, injury severity, time since injury, and pre/post-injury factors) will be tested and models augmented with terms for these confounders will be considered.

Puberty stage: in our primary analyses, we will use a binary puberty score (pre/post pubescence). Secondary analyses will consider each of the puberty measures (PDS, hormonal levels, Tanner stage) separately.

Neuropsychiatric outcomes: our primary analyses will use a composite global neuropsychiatric risk score based on the ASEBA Summary scales as our main outcome. In secondary analyses, we will consider each of the neuropsychiatric measures (IR, ASEBA, Emotional Regulation) separately.

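### The Aim 2 connectivity outcome is defined in two conflicting ways, and neither adjusts for the same girl's T0 connectivity

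*Protocol article*

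**What the plan says.** Under Research design, both scans are planned for every girl: "Participants will undergo an MRI protocol, a short neuropsychiatric assessment and a clinical assessment of puberty stage and hormonal level, across two time points".

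The Aim 2 paragraph of the Analytical approach is titled as the "effect of changes in puberty stage and hormonal levels on mediator and outcome". Its models are built in three steps, "controlling for age and pre/post-injury factors in the 1st step; for the injury severity in the 2nd step", and in the third step "puberty stage and hormonal levels at T0 and T1, as well as the difference between both measures". They are used "to predict (1) brain network connectivity and (2) neuropsychiatric outcomes, at T1 will be conducted". T0 connectivity appears in none of the steps.

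The section on changes in network brain connectivity defines the mediator differently: "A score indicating differences in brain network connectivity measures between T1 and T0 will be defined and used as the mediating variable in all analyses".

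No other section supplies the missing baseline. The Covariates section lists demographic factors, parental mental health and a CBCL completed at admission. The Secondary analyses section allows further confounder terms in all models, namely age together with "injury severity, time since injury, and pre/post-injury factors". T0 connectivity is in neither list.

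**The concern.** The puberty and hormone predictors use both time points, but on the Aim 2 wording the imaging outcome uses only the second scan. Two analysts following the article could fit different models, one to the T1 level and one to the T1 minus T0 difference. These answer different questions and can give different results.

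Two things are at stake. The first is precision: a measure that is stable within a girl leaves avoidable variance in the residual when its baseline is left out. The second, under a further condition, is attribution. If girls who differ in connectivity at T0 also go on to differ in pubertal change, in a way the other covariates do not capture, the T1-level model assigns that earlier difference to pubertal change.

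Only the connectivity regression is affected. The neuropsychiatric regression can use the CBCL from admission as its baseline.

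**Working it through.** **Inputs from the article (Sample size and power; Aims and hypotheses; Analytical approach).** Recruitment is 120, 60 per group. The stated minimum is 100, attrition about 20%, α 0.05, and the effect 13% of variance. The 120 is reproduced as 100 × 1.20. It was derived for Aim 1; no power figure is stated for Aim 2. Aim 2 is worded for pTBI girls only, giving 60 × 0.8 = 48. The Analytical approach says its analyses cover both groups, giving 120 × 0.8 = 96. Both are used below.

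**Assumptions.** The article gives no T0–T1 correlation of connectivity, so ρ is varied. In the formula below, ρ is the correlation left after the other model terms. The model is taken to have 8 terms without T0 connectivity and 9 with it. The term of interest has 1 degree of freedom and the test is two-sided.

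**Power on the T1 wording.** f² = 0.13/0.87 = 0.149. The noncentrality is λ = n·f² without T0 connectivity. With it, residual variance is multiplied by 1 − ρ², so λ = n·f²/(1 − ρ²). Power comes from the noncentral F distribution.

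For n = 48, λ = 48 × 0.1494 = 7.17. At ρ = 0.5 it becomes 7.17/0.75 = 9.56, and at ρ = 0.7 it becomes 7.17/0.51 = 14.06.

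| Variance explained | n | T1 only | + T0, ρ 0.3 | + T0, ρ 0.5 | + T0, ρ 0.7 |
|---|---|---|---|---|---|
| 13% | 48 | 74% | 78% | 85% | 96% |
| 13% | 96 | 96% | 98% | 99% | 99.9% |
| 8% | 48 | 51% | 55% | 63% | 80% |
| 8% | 96 | 82% | 85% | 91% | 98% |

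A Monte Carlo check at n = 48 and 13%, with six nuisance covariates, gave 66.8% to 69.2% (ρ 0.3), 66.1% to 77.5% (ρ 0.5) and 67.3% to 90.1% (ρ 0.7). Across this calculation and simulations with other covariate set-ups, the gains span about 2–4, 7–11 and 19–23 points.

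**The change-score reading.** With equal variances at T0 and T1, an unadjusted difference has residual variance 2(1 − ρ) relative to T1 alone: 1.4 at ρ 0.3, 1.0 at 0.5 and 0.6 at 0.7. Covariate adjustment gives 0.91, 0.75 and 0.51. At n = 48 and 13%, the change score has power of about 60%, 74% and 92%. So it does worse than T1 alone below ρ = 0.5 and worse than adjustment at each of these values.

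**Attribution.** The simulations generated T1 connectivity from T0 connectivity plus noise, with no effect of pubertal change given T0 connectivity.

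- *T0 puberty drives both T0 connectivity and later change (more mature girls have fewer stages left).* With T0 puberty in the model, as step 3 has it, the T1-only test rejects 4–6% of the time. Without T0 puberty it would reject 9–53%.
- *T0 connectivity still has a partial correlation of 0.2 with later pubertal change.* The T1-only test rejects about 6–13% at n = 48 and 6–21% at n = 96 for ρ 0.3–0.7. A leaner model with fewer covariates gave 9–16% and 17–28% for ρ 0.5–0.7.
- *With T0 connectivity added,* rejection is about 4–6%.
- *With an unadjusted change score,* it is 6–17% at n = 48 and 8–30% at n = 96, for partial correlations of 0.2–0.3 and ρ 0.5–0.9.

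**The case against.** The strongest reply is that the article does not commit to a T1-only analysis. The mediator section prescribes a difference score throughout, and the Aim 2 title calls connectivity the mediator. This stands. A reader might infer that the paired scans are simply analysed as one cross-section, but the documents show a conflict between two definitions. Aim 1 and the exploratory structural equation models also use connectivity change, so the study as a whole does not discard the baseline scans.

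A reader might also infer that baseline differences will routinely be credited to pubertal change, because more mature girls have fewer stages left. The documents do not support that. This path runs through T0 puberty, which is in step 3 with T0 hormones, and age is in step 1. High false-positive rates arise in models that leave T0 puberty out, and those are not the model described. This assumes that the steps are blocks entered in order, so that T0 puberty stays in. What remains is the case where T0 connectivity carries information on later pubertal change beyond those terms, for example because staging is coarse. The article neither shows nor excludes this.

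It can further be said that the Aim 2 hypothesis places the change in puberty and hormones and speaks of connectivity as higher or lower, so a T1 level is a legitimate outcome. That also stands. It does not argue against adjusting that level for its own baseline.

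Finally, the power gain rests on an unstated correlation and on n. At ρ = 0.3 it is minor, and at 13% of variance with 96 girls there is little power left to gain.

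**Conclusion.** The point holds as a conflict plus a missing baseline adjustment. The Aim 2 paragraph fixes a T1 outcome without T0 connectivity, the mediator section fixes a difference score, and neither conditions on the T0 scan. The choice should be settled before data are analysed, because the two readings differ in power and in what they estimate.

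The certain part is the inconsistency. The loss of precision on the T1 wording follows for any appreciable ρ, but its size does not: at 13% of variance and n = 48 it runs from 2–4 points (ρ 0.3) to 19–23 points (ρ 0.7). At n = 96 and the same effect it is about 1 to 4 points. Misattribution is conditional on T0 connectivity predicting later pubertal change given T0 puberty, hormones and age. Without that condition, the error rate stays near 5%. The simulated rates also define no effect as no effect given T0 connectivity, which is the question the proposed model asks.

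This concerns one of the two Aim 2 regressions and leaves the sized Aim 1 analysis untouched. It should be corrected, but it does not threaten the study's main analysis.

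**What to change.** State one Aim 2 connectivity outcome, in the same words, in the mediator section and the Aim 2 paragraph: the T1 value of each connectivity measure, with the T0 value of that same measure entered as a covariate in step 1, before the puberty and hormone terms. Limit the mediator section's difference score to the mediation analyses, so that "will be defined and used as the mediating variable in all analyses" no longer reaches the Aim 2 outcome.

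If the sponsor prefers to keep the difference as the Aim 2 outcome, adding T0 connectivity to that model gives identical puberty and hormone coefficients. Subtracting T0 from the outcome only lowers the T0 coefficient by one. The covariate is therefore the part that matters.

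The cost is one covariate and one degree of freedom. Girls with an unusable T0 scan drop out of this one model, as they would from any change-score analysis. No additional data are needed.
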